**Fig. 2 Fig2:**
[figure not shown]
Overview of the design of the HAYS study

The current study is part of a larger project in which a controlled clinical trial will take place to evaluate the effectiveness of an after school sports program following a standardized interval training in children and adolescents with a chronic disease or physical disability. This study, titled The Sport-2-Stay-Fit study (S2SF; Trialregister.nl registration number: NTR4698), will use the same outcome instruments (Zwinkels et al. 2015).

### Participants

Eligible for this study are all children and adolescents aged from 10 up to 19 years with a physical chronic disease or condition, including cardiovascular, pulmonary, musculoskeletal, metabolic or neuromuscular disorders. Table 1 shows the in- and exclusion criteria. Both children who are ambulatory or those propelling a wheelchair are eligible for this study. Participants have to understand the Dutch language, understand simple instructions and be able to perform a physical fitness test. Children and adolescents in electric wheelchair, having a progressive disease or participate in other research projects which might influence the current study results will be excluded. Contra-indications for performing an exercise test, based on the exercise pre-participation screening questionnaire, may lead to exclusion on the cardiopulmonary exercise test (Balady et al. 1998).

**Table 1 Tab1:** Eligibility and exclusion criteria

Eligibility	Exclusion
Children and adolescents with a physical disability or chronic disease: cardiovascular, pulmonary, musculoskeletal or neuromuscular disorder Children and adolescents between the age of 10 and 19 years Children and adolescents have to understand simple instructions Children and adolescents are able to perform physical fitness tests	Children and adolescents with progressive diseases Children and adolescents using an electric wheelchair During the length of the study, children are not allowed to participate in other research projects which might influence the current study results For the sporting group of the HAYS-study only: subjects who have not participated in any sports for the preceding 3 months No signed informed consent

Informed consent must be provided by all parents, as well as by subjects up from 12 years till 17 years. In line with Dutch law, no parental informed consent is required for subjects aged 18 years and over.

This study was approved by the Medical Ethics Committee of the University Medical Center Utrecht, the Netherlands.

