## Design

The HAYS study will be a cross-sectional study comparing children and adolescents with a physical disability or chronic disease, age 10–19 years, who are actively participating in organized sports to their non-sporting peers. The subjects who participate in sports will be matched on gender, age and diagnosis to their non-sporting peers, Fig. 2.

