### Recruitment

The children and adolescents will be recruited in the Netherlands among different patients associations, pediatric physical therapy practices, Wilhelmina Children’s Hospital in Utrecht, De Hoogstraat Rehabilitation Center in Utrecht, Fitkids, schools for children with a disability and sports clubs. Athletes will be recruited from a broad range of participation in sports: from recreational level to high level competitive sports.

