### Outcome measures

Table 3 shows an overview of the outcome measures and chosen measurement instruments in this study.

**Table 3 Tab3:** Overview of assessments used instruments, questionnaires and time schedule

Outcome measure	Parameter	Variable	Measurement	Time at location	Time at home
General	Demographics	DOB, Gender, Diagnosis, FMS score, activity level	General questionnaire		5 min
Cardiovascular health	Metabolic parameters	BMI	Height, Weight	5 min	
		Fat Free Mass	BIA		
		Blood pressure	Sphygmomanometer	10 min	
		Arterial stiffness Pulse wave velocity	Arteriograph		
Physical fitness	Aerobic fitness	VO_2peak_ RER Anaerobic threshold	CPET Shuttle run/ride test Bicycle test	30 min	
	Anaerobic fitness	Peak power Mean power	MPST	5 min	
	Muscle strength	Isometric muscle strength Explosive muscle strength	Grip strength Reverse curl Seated push up Standing broad jump or One stroke push	10 min	
	Flexibility		Modified Apley test Modified Thomas test	5 min	
	Agility		10 × 5 meter sprint	5 min	
Physical activity	Intensity	Heart rate	Actiheart	5 min	7 days
	Modality	Type of activity	Activ8 and Activity diary	5 min	7 days
Cognitive functioning	School performance	Educational level	Type of education Recent CITO-score	0 min	
	Attention	Focused attention Sustained attention Strategy Distractibility	Bourdon-Vos Cancellation task Capture task	15 min 5 min	
Injury and illness	Incidence injury and illness	Retrospective 3 months	Online questionnaire		3 min
		Longitudinal 1 year, every 2 weeks	Online questionnaire		
	Classification of injury or illness (if applicable)		Telephone conversation		5 min
Psychosocial health	Self-perception		Self-perception profile for children (SPPC)	10 min	
	Quality of life		Disabkids		10 min
	Self-efficacy		Exercise self-efficacy Scale		2 min
Total time				150 min	28 min

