#### School performance

The type of education of the participant will be noted. If available, outcomes of a national educational achievement test (CITO) will be used for quantifying school performance, in both ‘elementary school’ and ‘secondary school’.

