### Statistical analysis

Data will be checked for normal distribution before applying the right type of parametric or non-parametric tests. First, descriptive statistics will be used to describe the two samples. Independent sample T-tests or appropriate non-parametric tests will be used to to determine the differences between the sport and non-sport group.

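### No direct measure of intellectual level is collected, matched on or adjusted for, so attention and self-report contrasts could partly reflect a difference in intellectual ability between the groups

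*Protocol article*

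**What the plan says.** All places are in the protocol article.

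- **Eligibility (Participants and Table 1).** The text reads "Participants have to understand the Dutch language, understand simple instructions and be able to perform a physical fitness test". Table 1 repeats only the part on simple instructions: "Children and adolescents have to understand simple instructions". No upper or lower limit on intellectual level is given. Progressive disease and use of an electric wheelchair exclude.
- **Recruitment.** The sources include patient associations, a hospital, a rehabilitation centre and "schools for children with a disability and sports clubs".
- **Design.** Sporters "will be matched on gender, age and diagnosis to their non-sporting peers". The eligible diagnoses are physical ones.
- **General information and Table 3.** The characteristics listed are "DOB, Gender, Diagnosis, FMS score, activity level".
- **School performance.** "The type of education of the participant will be noted", and scores on a national achievement test are used where available. Table 3 places both under the cognitive functioning outcome.
- **Statistical analysis.** "Independent sample T-tests or appropriate non-parametric tests will be used" to compare the groups. No covariate is named.
- **Discussion.** The sport group is expected to show better cognitive functioning and school performance. The one source of bias that is worked through is the exercise-test modality.

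**The concern.** The comparison is observational. Intellectual level largely precedes a sports spell of three months or more. It plausibly affects who joins organised sport, and it plausibly affects timed attention tasks and the answering of multi-item questionnaires. A variable with those three properties is a confounder. Matching on a physical diagnosis removes the part of the imbalance that goes with diagnosis, but not the variation between children who share one.

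Attention is the only measure of cognition apart from school performance. If the two groups differ in intellectual ability, an unadjusted difference in attention scores cannot be separated from an effect of sport, and the same holds for the self-report scales. If nothing about intellectual disability is recorded at assessment, a later analysis plan cannot adjust for it directly.

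**Working it through.** **1. The plan's own figure.** This point disputes no figure; it uses 66 per group only as an input. From the Sample size section (mean 42, SD 8.2, difference 10 % = 4.2, alpha 0.05 taken as two-sided, power 0.80):

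n = 2 × (1.960 + 0.842)² × 8.2² / 4.2² ≈ 60 per group.

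The stated 66 follows if the difference is rounded to 4.0. The gap is on the safe side (power about 0.83 to 0.84 at 66) and has no bearing here.

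**2. Is intellectual level handled anywhere?**

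| Stage | What is stated | Intellectual level covered? |
|---|---|---|
| Entry | Dutch, simple instructions, fitness test | Only as a minimum |
| Matching | Gender, age, diagnosis | Only through diagnosis |
| General data | Birth date, gender, diagnosis, mobility score, activity | No |
| School data | Type of education; achievement test if available | Rough proxy, planned as an outcome |
| Analysis | Two-group tests | No |

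**3. How large could the effect be?** The documents give no share of children with lower intellectual ability and no size of deficit, so both are assumptions. Let Δp be the difference in that share between groups and s the deficit in SD units, with no true effect of sport.

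- Spurious difference: b = Δp × s.
- Standard error with 66 per group: √(2/66) = 0.174 SD.
- Two-sided 5 % rejection rate: Φ(b/0.174 − 1.96) + Φ(−b/0.174 − 1.96).

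Example: Δp = 0.20 and s = 1 give b = 0.20 and b/0.174 = 1.149. The rate is Φ(−0.811) + Φ(−3.109) ≈ 0.21.

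| Δp | s = 0.5 | s = 1.0 | s = 1.5 |
|---|---|---|---|
| 5 points | 5 % | 6 % | 7 % |
| 10 points | 6 % | 9 % | 14 % |
| 20 points | 9 % | 21 % | 41 % |
| 30 points | 14 % | 41 % | 73 % |

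**4. Check on the simplification.** The formula ignores the extra spread that the mixture itself creates. With shares of 30 % and 10 % and s = 1, the mixture SD is √(1 + (0.21 + 0.09)/2) = 1.07. The standardised difference falls to 0.20/1.07 = 0.19 and the rate from 21 % to about 19 %. The conclusion does not change.

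**5. Scale.** The difference detectable with 80 % power at 66 per group is (1.960 + 0.842) × 0.174 = 0.49 SD. The spurious differences for s = 1 and imbalances of 5 to 20 points are 0.05 to 0.20 SD. The calculation is symmetric: if the imbalance runs the other way, the bias has the same size but works against the sport group and could hide a real benefit.

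**The case against.** Several objections carry weight.

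- **A proxy is recorded.** A reader might infer that the study collects nothing bearing on intellectual level. It does: type of education is noted, and achievement scores where available. What is absent is a direct measure.
- **Entry is not open to everyone.** A reader might infer that any child who follows simple instructions is admitted. The language, fitness-test, progressive-disease and electric-wheelchair conditions also apply.
- **Direction is unknown.** It is tempting to say that the bias favours sport. The documents do not establish this. The Background itself cites Special Olympics participants with developmental disorders, who are in sport. A reversed or negligible imbalance is possible.
- **Not all outcomes are equally exposed.** The capture task compares reaction times with and without a distractor, which partly cancels general slowness. Questionnaire links go to participants or their parents. This narrows the concern but does not remove it for the other attention tasks or for self-report.
- **Adjusting the main model for type of education is doubtful.** It is a school-performance outcome that sport is hypothesised to improve, so conditioning on it could remove part of the effect sought. In this population, school placement may also reflect physical need. A gain in precision from such adjustment would rest on an explained variance that the documents do not give.
- **Covariates are often left to an analysis plan.** This is true, and the absence of a covariate list is not the point. An item that is not collected is different, because an analysis plan cannot restore it.

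**Conclusion.** The concern holds in limited form. No intellectual-level criterion is set beyond Dutch and simple instructions, matching does not cover intellectual level within a diagnosis, no direct measure is listed, and the stated analysis is unadjusted. The attention, self-perception, self-efficacy and quality-of-life contrasts are therefore open to confounding by intellectual ability.

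Size and direction cannot be determined from the documents. Under assumed imbalances of 5 to 20 points and a 1 SD deficit, the false-positive rate is about 6 % to 21 % with 66 per group. At the lower end this is close to the nominal 5 %, so the problem is material only if the imbalance is substantial. A firm claim that a favourable cognition result would be spurious is not supported. The affected outcomes are also not the one that sets the sample size, which is peak oxygen uptake. This is an inexpensive improvement to the design, not a fault that undermines the study.

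**What to change.** 1. Add one item to the general questionnaire: known intellectual disability, yes or no.
2. Report that item and type of education by group.
3. Report the attention, self-perception, self-efficacy and quality-of-life comparisons adjusted for the item and for gender, age and diagnosis, or show them with and without the children concerned.
4. Keep adjustment for type of education as a sensitivity analysis, for the reasons given above.

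The cost is one extra questionnaire item and one additional analysis, with no extra visit. Where the children concerned are left out, the sample shrinks: under assumed shares of 10 % and 30 %, 66 per group would become about 59 (66 × 0.9) and 46 (66 × 0.7). A yes/no item is coarse and leaves differences within the two categories unadjusted, so some confounding may remain and should be stated as a limitation.

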### Recruitment

The children and adolescents will be recruited in the Netherlands among different patients associations, pediatric physical therapy practices, Wilhelmina Children’s Hospital in Utrecht, De Hoogstraat Rehabilitation Center in Utrecht, Fitkids, schools for children with a disability and sports clubs. Athletes will be recruited from a broad range of participation in sports: from recreational level to high level competitive sports.

### Setting

This study is a collaboration between the exercise lab at the University of Applied Sciences Utrecht, Wilhelmina Children’s Hospital and De Hoogstraat Rehabilitation Center in Utrecht, the Netherlands.

### Procedures

Criteria for eligibility and exclusion of subjects are depicted in Table 1. After permission of the subject and when the subject is eligible to participate in the study, the subject is scheduled for the assessment. Thereafter a secured link to four of the questionnaires will be sent to the participants or their parents by email in order to fill out the questionnaires online 1 week before the first testing moment. The researchers will assess the subjects subsequently, once on physical fitness, cognition, psychosocial- and cardiovascular health. Physical activity will be monitored during 1 week. The incidence of injuries and illness will be monitored for the duration of 1 year, by sending a secured link to a 5-item questionnaire every 2 weeks by email. If an injury or illness is reported, a telephone conversation will follow, to get insight and to classify the sort of injury or illness. Table 2 shows the procedure for the principle researchers and the subjects in the HAYS study, from recruitment to the end of participation.

**Table 2 Tab2:**
[figure not shown]
Organisational and subject flow of the HAYS study

### Outcome measures

Table 3 shows an overview of the outcome measures and chosen measurement instruments in this study.

**Table 3 Tab3:** Overview of assessments used instruments, questionnaires and time schedule

Outcome measure	Parameter	Variable	Measurement	Time at location	Time at home
General	Demographics	DOB, Gender, Diagnosis, FMS score, activity level	General questionnaire		5 min
Cardiovascular health	Metabolic parameters	BMI	Height, Weight	5 min	
		Fat Free Mass	BIA		
		Blood pressure	Sphygmomanometer	10 min	
		Arterial stiffness Pulse wave velocity	Arteriograph		
Physical fitness	Aerobic fitness	VO_2peak_ RER Anaerobic threshold	CPET Shuttle run/ride test Bicycle test	30 min	
	Anaerobic fitness	Peak power Mean power	MPST	5 min	
	Muscle strength	Isometric muscle strength Explosive muscle strength	Grip strength Reverse curl Seated push up Standing broad jump or One stroke push	10 min	
	Flexibility		Modified Apley test Modified Thomas test	5 min	
	Agility		10 × 5 meter sprint	5 min	
Physical activity	Intensity	Heart rate	Actiheart	5 min	7 days
	Modality	Type of activity	Activ8 and Activity diary	5 min	7 days
Cognitive functioning	School performance	Educational level	Type of education Recent CITO-score	0 min	
	Attention	Focused attention Sustained attention Strategy Distractibility	Bourdon-Vos Cancellation task Capture task	15 min 5 min	
Injury and illness	Incidence injury and illness	Retrospective 3 months	Online questionnaire		3 min
		Longitudinal 1 year, every 2 weeks	Online questionnaire		
	Classification of injury or illness (if applicable)		Telephone conversation		5 min
Psychosocial health	Self-perception		Self-perception profile for children (SPPC)	10 min	
	Quality of life		Disabkids		10 min
	Self-efficacy		Exercise self-efficacy Scale		2 min
Total time				150 min	28 min

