#### General information

The participants’ characteristics such as date of birth, gender, medical diagnosis, functional mobility scale (FMS) score and type and frequency of sport activity will be identified by a general questionnaire. An exercise pre-participation screening questionnaire will inquire about possible factors influencing the outcomes of the test and the participants’ safety during the tests. These questionnaires will take approximately 5 min to be filled out by the participant and/or parent.

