## Discussion

The current paper describes the rationale, design and methods of a cross-sectional study concerning participation in sports focused on children and adolescents with a physical disability or chronic disease.

To our knowledge this is the first study to evaluate this effect of sport participation on physical, social and mental health within this population. The aim is to determine both the positive and negative effects of sports related to health outcomes in children with disabilities and chronic childhood onset conditions. We hypothesize that the group participating in sports regularly will show higher levels of physical activity associated with better health outcomes, a relative lower incidence density, better cognitive functioning and school performance.

New insights gained from this study could stimulate the improvement of facilities for adapted sports by the government. Also children with a chronic disease or physical disability and their caregivers, sport coaches, physical therapists and other interested parties will be more easily convinced of the advantages of sports participation for this population.

Although we carefully chose our study settings according to its population, we are aware of some limitations of the study.

Objective measurements are chosen where possible. To achieve the best results possible, the best fitting testing modality will be chosen for each participant. The testing modality has to mimic the type of sport participated in. In children who do not participate in sport, the most common form of physical activity in daily life will be chosen as an indicator for the test modality. In general, some test modalities have been proven to elicit a higher VO_2_ peak in the same subject (Bhambhani et al. 1992). The test modality could therefore influence the test outcome. To minimalize this bias we will pursue a comparable number of testing modality types in both groups.

In conclusion, this study will provide insight in the effects of sports participation on the health of children and adolescents with a chronic disease or physical disability.

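### No family socio-economic measure is named among the recorded characteristics or matching factors; unless one is collected, the cognition, school, psychosocial and BMI comparisons cannot be adjusted for family background

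*Protocol article*

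**What the plan says.** - **Characteristics recorded.** Table 3 (Outcome measures) lists under demographics "DOB, Gender, Diagnosis, FMS score, activity level". The General information section describes the same questionnaire: "The participants’ characteristics such as date of birth, gender, medical diagnosis, functional mobility scale (FMS) score and type and frequency of sport activity". The second list is worded as examples, and it names type and frequency of sport where Table 3 has activity level.
- **Family background.** Parental education, income and occupation are named nowhere in the article, and nor is any other family measure.
- **Matching.** The Design section says sporting participants are "matched on gender, age and diagnosis to their non-sporting peers".
- **Child's schooling.** The School performance section says "The type of education of the participant will be noted", with a national achievement test score if available. Both are recorded as outcomes.
- **Analysis.** The Statistical analysis section states "Independent sample T-tests or appropriate non-parametric tests will be used to" assess the differences between the two groups. It names no covariate.
- **Intended conclusion.** The aim is worded as determining effects of sport, and the Discussion hypothesizes "better cognitive functioning and school performance" in the sporting group. Its limitations paragraph treats test modality as a source of bias but does not mention family background.

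**The concern.** Sport participation is not assigned. It is reasonable to assume that regular organized sport for a child with a disability depends partly on family means, transport and support. It is also reasonable to assume that the same background is related to attention, school level, quality of life and BMI. Both are general assumptions, not statements in the article. If both hold, a sporting and a non-sporting group of the same gender, age and diagnosis could differ on these outcomes with no effect of sport at all.

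Matching on gender, age and diagnosis does not address this. Nor can the child's own school type stand in for family background, because it is one of the outcomes being compared. Mobility, another obvious difference between the groups, is at least recorded through the FMS and could be used in an analysis. For family background no recorded variable is named. What is at stake is the reading of the cognition and school hypotheses, and of the psychosocial and BMI comparisons, as effects of sport.

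**Working it through.** **Is a family measure named?**

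| Place in the article | What it covers | Family measure named? |
|---|---|---|
| Table 3, demographics | Birth date, gender, diagnosis, FMS, activity level | No |
| General information | Similar list, given as examples | No |
| Design, matching factors | Gender, age, diagnosis | No |
| School performance | Child's education type and test score, as outcomes | No |
| Statistical analysis | Two-group test, no covariate | No |

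This supports the statement that no such measure is named. Because the second list is illustrative, it does not show that none is collected.

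**How large could the distortion be?** The article gives no figure on this point, so there is none to reproduce. The only input from the document is the group size of 66 (Sample size section), taken as given. The other two inputs are assumptions:

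- *g*: difference between the groups in family background, in SD.
- *r*: change in the outcome, in SD, per SD of family background.

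Spurious difference: d = g × r.

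Non-centrality of the two-sample t-test with 66 per group: λ = d / √(2/66) = d / 0.174.

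The false-positive rate is the probability that a two-sided 5 % t-test with 130 degrees of freedom rejects when sport has no effect.

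| g (assumed) | r (assumed) | d = g × r | λ | False-positive rate |
|---|---|---|---|---|
| 0.2 | 0.1 | 0.02 | 0.11 | about 5 % |
| 0.3 | 0.2 | 0.06 | 0.34 | 6.4 % |
| 0.5 | 0.3 | 0.15 | 0.86 | 13.7 % |
| 0.5 | 0.4 | 0.20 | 1.15 | 20.7 % |
| 0.7 | 0.4 | 0.28 | 1.61 | 35.8 % |

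A normal approximation gives nearly the same values (13.8 % at 0.15 SD and 36.3 % at 0.28 SD). The range therefore runs from essentially nominal to seriously inflated. Nothing in the article says where this study lies.

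**The case against.** - **Absence from a condensed article is not absence from the study.** The General information list is illustrative, Table 3 is called an overview, and the two lists do not match item for item. The questionnaire and full protocol are not shown. This stands: a reader might infer that family background is not collected, but the article supports only that it is not named.
- **The gap can still be closed.** A reader might also infer that no later step could repair it. The article does not support that. Families receive a short questionnaire every 2 weeks for 1 year, with a telephone call when something is reported, and parental education changes little over such a period. What remains true is that no analysis can adjust for a variable that is never obtained.
- **The causal links, their direction and their size are assumed.** The Recruitment section lists sources but not which group each one supplies, so even the claim that the bias favours sport is a presumption. This stands, and small inputs leave the error rate near 5 %.
- **Covariates belong in an analysis plan.** This stands for the choice of covariates. It does not settle the point, because an analysis plan can use only variables that the study collects.
- **The outcome that sizes the study is peak oxygen uptake, which is not among the comparisons raised here.** This is correct, and it limits the reach of the point.

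**Conclusion.** The point holds in a limited form. As written, the plan names no family socio-economic measure among the recorded characteristics or the matching factors, and it states an unadjusted comparison of self-selected groups. Unless such a measure is obtained, differences in cognition, school performance, psychosocial outcomes and BMI cannot be adjusted for family background, although the article means to read them as effects of sport.

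The size is illustrative: about 5 % to 36 % false positives at 66 per group for assumed spurious differences of 0.02 to 0.28 SD. This rests on assumed imbalances and slopes, a two-sided t-test and no true effect. It shows that the matter could be negligible or important, not that these comparisons are distorted. Without the measure, the investigators could not tell which case applies. This is an inexpensive improvement to make; the omission does not invalidate the study.

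**What to change.** Add one item, the parents' highest completed education, to the general questionnaire and to the Table 3 demographics. For participants already assessed, ask it at one of the two-weekly contacts. Report it by group. Include it as a covariate, in a regression model suited to the outcome, in the comparisons of cognition, school performance, psychosocial outcomes and BMI. If it is already collected, say so and name it as a covariate.

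The cost is one question in a form of about 5 minutes that the participant and/or parent already completes, and one extra model term. Some families will leave it blank, so the number missing should be reported by group. Parental education is only a proxy for family means and support: adjustment reduces this confounding but does not remove it, and the report should say so.
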